##### In-hospital mortality

All-cause mortality will be recorded after 28 treatment days and at 3 months during the follow-up period.

##### SOFA questionnaire

The clinical symptom questionnaire for SCAP will be assessed at baseline, and at days 0, 4, 7, 14, and 28 of the treatment phase.

##### Community acquired pneumonia-clinician report outcome (CAP –CRO)

A CAP-specific disease activity score, daily function, and health state will be assessed at baseline, at days 4, 7, 14, 21, and 28, and at the follow-ups at 30, 60, and 90 days.

##### Health economics

The cost of the treatment phase will be recorded for the 28 days.

#### Adverse event reporting

Side effects and adverse effects of TCM treatment will be assessed with a questionnaire. Any adverse events will be listed in the trial record and followed up to completion by the trial coordinators and respiratory physicians. Adverse events will be scored using a six-point scale: 0 = none, 1 = minimal, 2 = mild, 3 = moderate, 4 = severe, and 5 = extremely severe. Participants can report adverse events at any time throughout the trial and will receive advice accordingly. Serious adverse events will be reported to the reviewing human research ethics committee and the site ethics committees within the timeframe specified by the lead ethics committee. Throughout the study period trial, coordinators will contact the participant’s usual treating doctor to record relevant data on presentations.

Participants may withdraw from the study for any reason at any time without repercussions. They will be withdrawn by investigators only if it is deemed medically unsafe for them to continue. Dropouts will not be replaced.

#### Sample size considerations

This study is designed to show the superiority of the TCM group compared to placebo treatment. Our primary hypothesis is that adjunct TCM treatment in patients with SCAP will result in reduced treatment failure compared to the placebo. To estimate the frequency of our primary endpoint, we used data for SCAP patients from completed studies [12]. Based on these previous trials, we assumed a treatment failure rate of 30% in the placebo group and 10% in the adjunct TCM group over 28 days. Thus, a sample size of 198 patients is needed to achieve a statistical power of 90% (two-sided type-1 error of 5% in both scenarios). We intend to recruit 198 study patients from July 2017 to December 2019.

#### Intention-to-treat and per-protocol population

Following the intention-to-treat principle, all patients receiving at least one dose of study medication will be included in the analysis with group allocation as randomized. Patients found to have violated the inclusion criteria or met the exclusion criteria due to information that was not available at study entry will be excluded post randomization. Criteria for excluding patients from the per-protocol analysis are, in addition, withdrawal of informed consent or non-compliance with the study medication or the concomitant procedures. Therefore, patients stopping or pausing the study medication at any time will not be considered in the per-protocol analysis. A patient will not be followed up for any study measure if they withdraw informed consent. In all other cases, the follow-up will be performed as planned.

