### Outcome measures

#### Primary outcome measure

The primary endpoint is treatment failure, which includes treatment failure that occurred early or late. Early treatment failure is defined as clinical deterioration within 72 h of treatment (including shock, need for invasive mechanical ventilation not present at baseline, or death). Late treatment failure is defined as radiographic progression (increase of ≥50% of pulmonary infiltrates compared with baseline), persistence of severe respiratory failure (ratio of PaO_2_ to fraction of inspired oxygen < 200 mmHg with respiratory rate ≥ 30 breaths/min in patients not intubated), need for invasive mechanical ventilation not present at baseline, or death 72 h after treatment initiation. These criteria have been used previously with modifications [12].

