#### Statistical analysis

A descriptive statistical analysis will be performed for all study variables. We will calculate the mean, median, and standard deviation for quantitative variables, and the absolute and relative frequency for qualitative variables. We will use SPSS 19.0 (SPSS Inc., Chicago, Illinois, United States) to analyze the data statistically. An intention-to-treat analysis will be applied using the last observation carried forward method for missing data. Analysis of covariance with the baseline as the covariate will be used to assess differences in treatment outcomes between the two groups at each of the time points. To correct for an inflated risk of type 1 errors, multiple comparison procedures suggested by Ludbrook et al. [14] will be used for the outcome measure by using it as a covariate in the statistical analysis. A data safety monitoring board has been established to assess the progress of the trial, particularly the safety endpoints.

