## Discussion

Despite advances in treatments with antimicrobial agents, mortality among hospitalized patients with SCAP is still high. SCAP remains the leading cause of death in the world [15]. TCM have been used for thousands of years in China for treating pneumonia, and it is widely used in many countries. Evidence from both clinicians and patients suggests that TCM may improve SCAP survival rates. However, the available evidence has been derived from only a few small randomized controlled trials.

Some studies have shown that TCM may have a beneficial effect on patients with CAP, including those with severe pneumonia [16]. In these patients, reviews show that TCM may reduce either length of hospital stay or mortality without causing complications [17]. However, insufficient data on SCAP are available, and the treatment in some studies was not according to syndrome differentiation. In view of these findings, a large prospective and adequately powered trial should conclusively determine the risks and benefits of adding TCM according to syndrome differentiation to the treatment of patients with SCAP.

In the current trial, we will include SCAP (risk class V in the pneumonia severity index) requiring hospitalization. According to previous studies, our study may not be powered to show a survival benefit. Our primary endpoint will be the rate of treatment failure, which includes treatment failure that occurred early or late. These criteria have been used previously with modifications.

Our secondary endpoints will be time to clinical stability, as defined by the guidelines of the Infectious Diseases Society of America and the American Thoracic Society, as well as length of intensive care unit and hospital stays, and in-hospital mortality.

In our study, we will administer an oral TCM granule for 28 days. All patients will be treated with antibiotics according to international guidelines. The treatment group will receive TCM according to the TCM syndrome. The control group will receive TCM placebo according to the TCM syndrome. Because a variety of treatment options have been adopted, we use the single blind method. We opted for an oral formula, since by choosing a uniform application formula, further bias can be prevented. Furthermore, the use of the placebo ensures the blinded design of this trial. Strict randomization will be implemented to minimize selection and evaluation bias.

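### The set called intention-to-treat leaves out undosed patients and removes others after randomisation on later-learned ineligibility, with no stated safeguard against selection related to outcome

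*Protocol article*

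**What the plan says.** The section on the intention-to-treat and per-protocol population names the intention-to-treat principle and then sets two limits on it. The first is a dose condition: "all patients receiving at least one dose of study medication will be included in the analysis with group allocation as randomized". The second is a removal rule, under which "Patients found to have violated the inclusion criteria or met the exclusion criteria due to information that was not available at study entry" are taken out after randomisation.

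The per-protocol rule follows directly: "Criteria for excluding patients from the per-protocol analysis are, in addition, withdrawal of informed consent or non-compliance with the study medication". The Statistical analysis section then states which analysis is used: "An intention-to-treat analysis will be applied using the last observation carried forward method for missing data".

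Three other places bear on the point:

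- The exclusion list under Study setting and participants contains a criterion on hospital discharge within 2 days and on needing an operation.
- The primary outcome begins to count at once: "Early treatment failure is defined as clinical deterioration within 72 h of treatment".
- On blinding, the Discussion says: "Because a variety of treatment options have been adopted, we use the single blind method".

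**The concern.** An intention-to-treat comparison is protected because nothing that happens after allocation decides who is counted. Here two things can: whether a dose was taken, and whether information learned later makes the patient ineligible.

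The second is the more serious. Several listed exclusions (aspiration, fungal or tuberculous disease, abscess, tumour) are diagnoses that may be confirmed only after entry. A patient who is failing may be investigated more closely than one who is recovering. If so, removal is related to the primary outcome. If the arms differ in how often this happens, or if knowledge of the arm influences the ruling, the failure rates are no longer a randomised comparison.

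The wording on discharge and operation may add to this. If it covers events after entry, the rule also removes patients for things that happen after randomisation, and a 2-day discharge falls inside the 72 h window for early failure. Shorter hospital stay is one of the trial's hypotheses, so such removal could depend on treatment.

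**Working it through.** **1. Does the removal apply to the intention-to-treat set?** The eligibility removal comes before the per-protocol sentence, which introduces its own criteria as additional. The per-protocol set is therefore the intention-to-treat set less further patients, and the eligibility removal has already been made. The Statistical analysis section uses that intention-to-treat set. The label and the rule do not agree.

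**2. The plan's own figure.** Sample size considerations gives 30% vs 10% failure, two-sided 5%, 90% power and 198 patients (99 per arm). With the pooled formula,

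n = [1.960·√(2·0.2·0.8) + 1.282·√(0.3·0.7 + 0.1·0.9)]² / 0.2² = (1.109 + 0.702)² / 0.04 ≈ 82 per arm, or 164 in total.

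With continuity correction the result is 92 per arm (184). The 198 is not reproduced from the stated inputs without an inflation that the article does not give. This matters here only because it leaves a margin: power at 99 per arm is 0.946.

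**3. Assumed extreme, no true effect.** The document gives no exclusion rate, so the counts below are assumptions. Start from 30/99 = 30.3% failures in each arm.

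| Failures removed (arm A / arm B) | Arm A | Arm B | Spurious difference |
|---|---|---|---|
| 5 / 0 | 25/94 = 26.6% | 30.3% | 3.7 points |
| 10 / 0 | 20/89 = 22.5% | 30.3% | 7.8 points |
| 10 / 5 | 20/89 = 22.5% | 25/94 = 26.6% | 4.1 points |
| 5 / 5 | 26.6% | 26.6% | 0 |

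The 7.8 points are 7.8/20 = 39% of the planned 20-point effect. By normal approximation with a true 30% in both arms, removing failures equal to 5%, 10% or 15% of the TCM arm only leaves an apparent rate of (0.30 − f)/(1 − f) = 26.3%, 22.2% or 17.6%. The two-sided rejection rate rises from 5% to 8.7%, 22.5% or 49.3%.

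**4. The opposite direction.** Suppose early discharges, all non-failures, are removed. An arm with failure rate p that loses a fraction e then shows p/(1 − e).

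- True 30% vs 10%, with 10% removed from TCM only: 30.0% vs 0.10/0.90 = 11.1%. The difference is 18.9 points and power 0.898.
- True 30% vs 10%, with 5% removed from control and 20% from TCM: 31.6% vs 12.5%. The difference is 19.1 points and power 0.859.
- No true effect, with 10% removed from control only: 33.3% vs 30.0%. Rejection is 7.8%.

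**5. Equal removal, unrelated to prognosis.** The rates stay at 30% vs 10% and only the numbers fall. Power is 0.935 at 94 per arm, 0.922 at 89, 0.907 at 84 and 0.889 at 79.

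**The case against.** The strongest reply concerns the discharge and operation criterion. A reader might infer that the plan certainly deletes patients who go home within 2 days of randomisation. The text does not establish that. The discharge line is in the past tense and can mean a recent discharge before enrolment; the criterion on participation in other studies also looks back. Need for an operation can be judged at screening. The removal rule itself can be read as covering facts that were true at entry but not yet known, such as a pending HIV or tuberculosis result. This objection stands, and that part of the point is conditional on the reading.

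Even on the broader reading, the numbers may be small. The trial enrols severe pneumonia, and discharge is recommended only after at least 24 h of stable vital signs. Length of stay is defined by objective readiness for discharge, so actual early discharges do not map directly onto that endpoint.

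A reader might also infer that the rule favours TCM, or that eligibility is ruled on by people who know the arm. Neither is supported. The bias can run either way. The article describes a placebo and a double-dummy design and does not say who is blinded or who decides eligibility. That failing patients are investigated more is plausible, but no source in the document shows it.

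Finally, apart from withdrawal of consent, follow-up is to continue as planned. Outcomes of removed patients should therefore exist, so an analysis of all randomised patients remains feasible. That makes the repair easy but does not change the stated analysis set. An unseen analysis plan might add a blinded review, but the article's removal rule carries no such condition.

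**Conclusion.** The point holds in this form: the set called intention-to-treat is not one, and its post-randomisation removal rule has no stated safeguard in a single-blind trial. It should be corrected because it governs the primary comparison. The dose condition is the smaller part, and its effect depends on how many patients go undosed and on who knows the arm before the first dose.

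Neither the size nor the direction of the bias can be derived from the document. The 3.7 and 7.8 points are an assumed extreme in which every removed patient is a failure and all come from one arm; they are not a forecast. Balanced removal costs mainly power, and on the protocol's assumed rates power stays above 90% down to 84 per arm. The further concern about removal inside the 72 h window depends on reading the discharge and operation criterion as covering events after entry.

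**What to change.** Define the primary analysis set as all randomised patients in the arm allocated, whether or not dosed and whatever is learned later. Move the at-least-one-dose condition and the later-found-ineligible exclusion to the per-protocol set or to a sensitivity set. For any such set, limit the exclusion to ineligibility that existed before randomisation, judged blind to arm and outcome.

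State that the discharge and operation criteria apply only as known before randomisation and are not grounds for removal from the primary analysis.

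This is a wording change. It needs no extra patients, and at 99 per arm power is 0.946 on the assumed rates. The downside is that a few ineligible or undosed patients stay in and may slightly dilute the effect.

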### Study setting and participants

All adult patients with SCAP at respiratory departments in 11 tertiary-care hospitals will be screened and enrolled. Eligible patients will be asked for their informed consent and then centrally randomized to either the integrated traditional Chinese and conventional medicine group or to the conventional medicine group in a ratio of 1:1. All medications will be taken orally for 28 days. If the patient is not able to give informed consent at the time of hospitalization due to the severity of their CAP, informed consent from their next of kin and an independent physician will be obtained. In these cases, informed consent from the patient will be obtained as soon as possible. Patient recruitment started in July 2017 and is planned to be completed in December 2019.

To be included, patients must be aged between 18 years and 80 years, and must meet the criteria for SCAP (defined with the modified American Thoracic Society criteria) [11] and the criteria for TCM syndromes. TCM syndrome differentiation relates to pathological changes: phlegm-heat obstruction in the lung, pulmonary stagnation of phlegm, pathogenic heat trapped in the pericardium, or pathogenic depression.

The following patients are excluded:Pregnant and lactating womenPatients with trauma, hematologic malignancies, various solid tumors, obstetric complications, aspiration pneumonia, fungal pneumonia, HIV-related pneumocystis carinii pneumonia, tuberculosis, bronchiectasis with infection and a pulmonary abscess, dementia, mental illness, neuromuscular disorders affecting the respiratory motor function, severe cardiovascular disease, severe liver disease, or kidney diseasePatients who are unwilling to cooperatePatients who were discharged from hospital within 2 days or require an operationPatients with severe immunosuppression (due to HIV infection, immunosuppressive conditions, or medication).Patients who have participated in other clinical studies in the past 4 weeksPatients unwilling to sign the informed consent.

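### The per-protocol rule has no exemption for death or for stopping because of treatment failure, so membership of that set depends on the primary outcome

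*Protocol article*

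**What the plan says.** All of the following is in the protocol article.

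- **Intention-to-treat and per-protocol population.** Beyond the exclusions that apply to the intention-to-treat set, patients leave the per-protocol set for withdrawn consent or for "non-compliance with the study medication or the concomitant procedures". The article draws the consequence that "patients stopping or pausing the study medication at any time will not be considered in the per-protocol analysis". No exception follows. The same section continues follow-up as planned for everyone who has not withdrawn consent.
- **Primary outcome measure.** Early failure is clinical deterioration within 72 h, "including shock, need for invasive mechanical ventilation not present at baseline, or death". Late failure includes "need for invasive mechanical ventilation not present at baseline, or death 72 h after treatment initiation". It also includes radiographic progression and persistent severe respiratory failure in patients who are not intubated.
- **Study setting and participants.** "All medications will be taken orally for 28 days".
- **Adverse event reporting.** On withdrawal of participants: "They will be withdrawn by investigators only if it is deemed medically unsafe for them to continue".
- **Statistical analysis.** The only analysis named is intention-to-treat.

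**The concern.** A per-protocol set should be defined by adherence to the assigned treatment, not by the outcome. This rule turns on whether dosing was ever interrupted, and some primary events end dosing by their nature. A patient who takes every dose due and dies on day 10 has stopped before day 28. On the literal wording that patient is excluded, and the primary event goes too. The same happens to a patient who reaches any failure component and stops later.

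Follow-up continues after stopping, so these outcomes are expected to be known. The rule would discard observed failures rather than deal with missing ones.

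At stake is the use of the per-protocol result as a check on the main analysis. If the two disagree, a reader could not tell an effect of adherence from an effect of removing failures.

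**Working it through.** **Planning figures.** Sample size considerations gives failure rates of 30% (placebo) and 10% (TCM), two-sided alpha 5%, power 90% and 198 patients, that is 99 per arm at 1:1. With the usual normal approximation:

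n per arm = [1.96·√(2·0.20·0.80) + 1.2816·√(0.30·0.70 + 0.10·0.90)]² / 0.20² = (1.1087 + 0.7019)² / 0.04 ≈ 82

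This gives 164 in total, or 184 with continuity correction (92 per arm). The stated 198 is not reproduced. It exceeds what the stated inputs need and gives about 94.6% power. That gap does not bear on this point; 99 per arm is used below only as the starting size.

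**Model.** Let p be the true failure rate in an arm and f the share of failures who stop or pause and are dropped. The article does not give f, so a range is shown. Assume that no non-failures are dropped.

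- Per-protocol failure rate = p(1 − f) / (1 − pf)
- Per-protocol odds = p(1 − f) / (1 − p), which is the true odds multiplied by (1 − f)

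**Equal f in both arms**, starting from 29.7 and 9.9 expected failures:

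| f | Placebo | TCM | Difference | Failures left (placebo, TCM) |
|---|---|---|---|---|
| 0 | 30.0% | 10.0% | 20.0 points | 29.7, 9.9 |
| 0.25 | 0.225/0.925 = 24.3% | 0.075/0.975 = 7.7% | 16.6 points | 22.3, 7.4 |
| 0.5 | 0.15/0.85 = 17.6% | 0.05/0.95 = 5.3% | 12.4 points | 14.9, 5.0 |
| 0.8 | 0.06/0.76 = 7.9% | 0.02/0.92 = 2.2% | 5.7 points | 5.9, 2.0 |
| 1 | 0% | 0% | 0 | none |

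Normal-approximation power falls from 94.6% at f = 0 to about 88% at f = 0.25, 75% at f = 0.5 and 48% at f = 0.75.

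The odds ratio does not move. It is (0.10/0.90)/(0.30/0.70) = 0.259 at f = 0 and (0.05/0.90)/(0.15/0.70) = 0.259 at f = 0.5, because the factor (1 − f) cancels. It is undefined only at f = 1, where no events remain.

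**Unequal f.** The odds ratio is multiplied by (1 − f_TCM)/(1 − f_placebo). With assumed values of 0.5 and 0.8:

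- f_TCM = 0.5, f_placebo = 0.8: 0.259 × 0.5/0.2 = 0.65, and the rates are 7.9% vs 5.3%.
- f_TCM = 0.8, f_placebo = 0.5: 0.259 × 0.2/0.5 = 0.10, and the rates are 17.6% vs 2.2%.

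The bias can run towards or away from no effect.

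**The case against.** The strongest reply is that the sentence follows from a non-compliance criterion and only spells it out. Dying on treatment is not ordinarily non-compliance, so the authors may never have meant to exclude deaths. That is a fair reading of intent. The wording is unqualified, though, and an analyst who applies it as written would drop deaths. Nor is the point simply left open for the analysis plan: the article states a working rule.

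Several stronger readings are tempting, and the article does not support them.

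- **That intubated or shocked patients are removed.** The article nowhere says that either event interrupts study medication. Oral dosing makes it plausible. However, the Study protocol section and the Discussion also provide for injections in two syndromes, which conflicts with the oral-only statement and must be reconciled separately. Only death follows directly from the text.
- **That the rule deletes the primary events altogether.** Radiographic progression and persistent respiratory failure without intubation need not interrupt dosing. Rates near zero arise only as f approaches 1.
- **That the treatment effect collapses.** With equal f this is true of the absolute difference and of precision, but not of the odds ratio.
- **That patients who stop for harm are hidden.** Adverse events are recorded and followed to completion whatever the analysis set, and dosed patients who stop remain in the intention-to-treat set.
- **That the trial's main conclusion is at risk.** The article nowhere makes the per-protocol analysis primary or rests a decision on it.

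**Conclusion.** The point stands as a defect in the definition of a secondary population. As written, the rule excludes patients who die before day 28 and anyone who stops at, after or because of treatment failure, so selection into the set depends on the outcome.

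The size depends on f, which is assumed and not documented. With equal f, the 20-point difference becomes 12.4 points at f = 0.5 and 5.7 points at f = 0.8, with fewer events and the odds ratio unchanged at 0.26. Bias in the odds ratio needs f to differ between arms; with assumed values of 0.5 and 0.8 it ranges from 0.10 to 0.65. These figures rest on the planning rates, on 99 patients per arm and on no removal of non-failures. The intention-to-treat analysis keeps the events that this rule drops.

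**What to change.** Reword the per-protocol definition so that adherence is assessed only up to the first of primary event, death or day 28. State that stopping or pausing at, after or because of the primary event is not non-compliance and does not exclude a patient. If a minimum adherence is wanted, the sponsor should prespecify it; the article gives no basis for a particular threshold. Settle this before the data are analysed.

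The cost is minor rewording and use of dosing dates alongside event dates when the set is built. Treatment, visits and sample size do not change.
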